### Study assessments

The GFR of the renal allograft is the ultimate parameter that describes acute and chronic aspects of the graft function and is the most widely used measure for the outcome in renal transplantation studies. Sensitivity of the GFR can be improved by using the patients’ individual percentage change in GFR in a defined time interval (“delta GFR”). The primary objective is to show that additional anti-rejection treatment with rituximab is more efficacious than the standard anti-rejection treatment with regard to the allograft function one year after these treatments. For this purpose, individual changes in the glomerular filtration rate (GFR) will be determined using the baseline GFR before the rejection and the value at one year after rejection treatments. The GFR will be calculated using the simplified MDRD formula (eGFR = 186*(0.742 for females)*creatinine-1.153*age −0.203)
[20].

As a second endpoint, interstitial fibrosis and tubular atrophy (IF/TA) will be used as an indicator of established chronic damage. To achieve maximum possible accuracy, biopsy specimens will be stained for fibrosis (Sirius Red) and quantified by computerized image analysis in specified areas of the renal tissue (renal cortex).

Again, to enhance the informational value of this parameter, the patient’s individual change of IF/TA in the initial biopsy at the time of acute rejection and inclusion in the study to the biopsy at the end of the study will be used (“delta-IF/TA”).

To assess the safety of the intervention, occurrence and frequency of adverse events in both treatment groups will be analyzed. These include the patient’s self-reported events and those inquired about by the study physician during regular study visits or obtained from additional in- and outpatient attendances. As a combined secondary safety endpoint, further rejection episodes, terminal graft failure during the observation period, severe infections and patient deaths will be analyzed.

### Ethics statement

The study was approved by the ethics committee of Hannover Medical School as the leading center and the Paul Ehrlich Institute, as well as by all local ethics committees of the participating centers.

### Statistical analysis

The primary analyses will be performed in all patients who have received a least one dose of the study medication. Sensitivity analyses will be performed in the per protocol population, including all patients that finish the study at the last visit one year after study entry. The change in GFR between baseline and the assessment one year after the rejection episode will be performed with ANCOVA analysis adjusted for baseline, treatment and center. One interim analysis and one final analysis will be performed in this trial following the aforementioned decision rules (see Sample size calculation).

As soon as it can be demonstrated that rituximab is superior to placebo with respect to the primary endpoint, the secondary endpoint progression of interstitial fibrosis and tubular atrophy will be assessed in a confirmatory sense. Increase of fibrotic and atrophic interstitial area is analyzed with ANCOVA with treatment, center and baseline IF/TA in the first biopsy included as co-variates. Subanalyses will include the effect of rituximab in patients with different severity grades of rejection (Borderline, Type I and II), different immunosupression before inclusion in the study and patient groups receiving one versus two applications of rituximab. Frequency of adverse events will be reported per treatment group and analyzed with a chi-square test. *P*-values will be assessed descriptively.

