## Design

### Study design

The RIACT-study is a randomized, double-blind, placebo-controlled, parallel group multicenter Phase III study. The study hypothesis is that treatment with rituximab in addition to the standard therapy with steroid-boli is superior to the standard therapy in acute T-cell mediated tubulointerstitial rejections in which B-cell infiltrates are present. The primary efficacy endpoint of the study is the change of the glomerular filtration rate (GFR) one year after intervention compared to the baseline GFR before the rejection episode.

Secondary endpoints are: 1) the progression of interstitial fibrosis and tubular atrophy (IF/TA) between the allograft biopsy that led to enrollment in the study and a scheduled protocol biopsy one year after intervention and 2) safety and side effect aspects of rituximab in kidney transplanted patients.

The study is recruiting a total of 180 patients with an acute T-cell mediated tubulointerstitial rejection who also show significant B-cell infiltrates in their biopsies, defined as >30 CD20+cells/hpf. After diagnosis of a B-cell-rich acute T-cell mediated tubulointerstitial rejection and informed consent (run-in phase), the patients will be centrally randomized for double-blinded treatment with rituximab or placebo, which will be given in addition to the standard anti-rejection therapy with steroid boli (study phase).

During the study phase a sufficient B-cell depletion (<5 B-cells/μl peripheral blood) after the first application of rituximab will be confirmed by fluorescence activated cell sorting (FACS) analysis. Patients with rituximab treatment and insufficient B-cell depletion undergo a second intervention with the same dose of rituximab. If a follow-up B-cell count in these patients reveals B-cells numbers above the target value, these patients will be excluded from the study. The follow-up period after intervention is 12 months. At this time, the primary endpoint renal allograft function change is determined, along with the secondary endpoints as safety parameters and degree of renal allograft fibrosis and tubular atrophy in a protocol biopsy.

The trial flow is outlined in Figure
1.

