### Inclusion and exclusion criteria

The population of renal allograft recipients is heterogeneous (for example, age, gender, first or repeated transplant, immunological risk), yet, all patients are at risk for acute rejection. Therefore, the inclusion criteria in the RIACT–trial are laid down in a way that allows as many patients as possible to participate in this study unless medical reasons advise against inclusion. Included are all female and male patients aged 18 years or older with the diagnosis of a T-cell mediated acute tubulointerstitial rejection (Banff IA/IB, or borderline rejection with simultaneous increase of creatinine of ≥20% over baseline creatinine before the borderline finding), and B-cell infiltrates, defined as more than 30 CD20+cells/hpf. All immunosuppressive regimens according to local transplant center standards at the time of rejection diagnosis are acceptable, except previous use of rituximab to have the obtained results applicable to a broad patient population. Patients with a humoral rejection (morphological signs of glomerulitis/capillaritis, positive C4d staining) and patients with positive SV40 staining as a sign of polyomavirus-infection are not eligible. The acute rejection must be diagnosed between 6 weeks and 12 months after kidney transplantation. The baseline allograft creatinine clearance (calculated by the abbreviated MDRD formula
[20]; before the rejection has to be over 25 ml/min. At screening, women of child-bearing age must have a negative pregnancy test, must not be nursing and have to agree in using adequate contraception throughout the study.

Patients are not eligible for the study entry if they had previous adverse reactions against anti-CD20 antibodies, have received rituximab within 12 months prior to the planned inclusion in the RIACT study, have any active infections (for example, active CMV, HIV or replicative hepatitis B or C infection), or had a splenectomy. Reasons for exclusion also include malignant tumors, cardiac diseases, such as heart insufficiency (New York Heart Association (NYHA) III-IV) or severe arrhythmia (Table
1).

**Table 1 T1:** Main inclusion and Exclusion criteria

	
Inclusion criteria	1. Kidney transplantation >6 weeks and <12 months before randomization
	2. Age ≥18 years
	3. Presence of an acute T-cell mediated tubulointerstitial rejection (Banff IA or IB) or Banff borderline rejection with simultaneous serum creatinine increase of ≥20% over baseline

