### Interventions and study plan

The diagnosis of an acute T-cell mediated tubulointerstitial rejection (Banff IA/IB) or a Banff borderline rejection with significant numbers of B-cells in the infiltrates is one of the major inclusion criteria for the RIACT study. To ensure a timely beginning of the anti-rejection therapy, the histopathological diagnosis will be made by the pathologists who are usually consulted by each participating center for kidney biopsy evaluation (all pathologists are in university departments). To achieve the highest degree of comparability and to reduce inter-center variability in the histopathological diagnosis, all pathologists will be provided with the same automated immunohistochemical staining platform (BondMaxTM, A. Menarini Diagnostics, Berlin, Germany). The stainings will be performed using the same stainer program and the same antibody- and staining-solutions. For the screening, the biopsies will be stained for CD20, C4d and SV40 in the above described fashion, in addition to the normal chemical stainings performed in each center for the rejection diagnosis.

All patients that fulfill the medical inclusion criteria and the histological inclusion criteria are asked to participate in the RIACT-study. After obtaining their written informed consent, patients attend a screening visit. At this visit the patients are asked to provide a medical history (with emphasis on the transplant history) and undergo a physical examination. Vital signs are measured and blood samples are taken to determine creatinine, cystatin C, electrolytes, liver enzymes and blood counts, including B-cell count by FACS-analysis. Furthermore, a urine status will be assessed (leukocytes, nitrite, protein, haemoglobin). To exclude pregnancy at the time of inclusion, ß-HCG-levels in female patients are measured. According to the standard therapy protocol for acute T-cell mediated tubulointerstitial rejection, all patients will receive the first, out of three, steroid bolus upon detection of B-cell infiltrates in the biopsy (defined as more than 30 CD20^+^-cells/hpf), patients enter the double-blind treatment period by randomization to treatment with either (A) standard treatment (two more steroid boli for the next two days) plus placebo (500 ml NaCl0,9%), or (B) standard treatment (steroid boli for the next two days) and the study drug, a single dose intravenous infusion of rituximab (375 mg/m^2^).

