Visit 1 (Day −1/-3 (prestudy))	-written consent
	-physical examination
	-laboratory tests
	-B-cell count
	-assessment of allograft function
	-beginning of rejection therapy (steroids) according to center standards
	-randomization
Visit 2 (Day 0)	-rituximab or placebo + standard concomitant medication
Visit 3 (Day 1)	- physical examination
	- patient history for specific side effects
Visit 4 (Day 35 ± 7)	- physical examination
	- laboratory tests
	- B-cell count
Visit 4a: if no complete B-cell depletion (<5/μl) is achieved:	second application of study medication or placebo (Visit 4a))
Visit 4b: (if study medication was administered in Visit 4a):	- physical examination
	- patient history for specific side effects
Visit 4c: (if study medication was administered in Visit 4a):	- physical examination
	- laboratory tests
	- B-cell count
Visit 5 (Day 182 ± 28)	- physical examination
	- laboratory tests
	- B-cell count
	- assessment of allograft function
Visit 6 (Day 356 ± 28)	- physical examination
	- laboratory tests
	- B-cell count
	- assessment of allograft function
	- re-biopsy

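### The primary ANCOVA leaves out the Visit 1 eGFR, which is available before study drug; this gives up precision of unknown size but causes no bias and no shortfall in stated power.

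*Protocol article*

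**What the plan says.** Study design defines the primary endpoint as "the change of the glomerular filtration rate (GFR) one year after intervention compared to the baseline GFR before the rejection episode". Study assessments repeats this: individual changes "will be determined using the baseline GFR before the rejection and the value at one year after rejection treatments". Baseline in the primary endpoint is thus the pre-rejection GFR, not a value taken at enrolment.

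Statistical analysis fixes the covariates of the primary model: the comparison "will be performed with ANCOVA analysis adjusted for baseline, treatment and center".

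Graft function is also recorded between the onset of rejection and study drug. Table 2 (Interventions and study plan) lists "assessment of allograft function" under Visit 1, one to three days before the infusion, with randomization as the last item of that visit. The text of the same section says that at screening "blood samples are taken to determine creatinine, cystatin C, electrolytes, liver enzymes and blood counts". An eGFR can be calculated from that creatinine with the formula in Study assessments.

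Sample size calculation uses an unadjusted t-test and expects the adjusted analysis to add power, without saying how much.

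**The concern.** The one-year change runs over a period that begins before the patient enters the trial. By Visit 1 part of it has already happened, and treatment cannot alter that part. Patients also differ in how far they have fallen by then. A borderline case qualifies only as a "borderline rejection with simultaneous increase of creatinine of ≥20% over baseline creatinine before the borderline finding", while Banff IA and IB cases need no creatinine rise at all.

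To the extent that the early loss persists to one year, it adds between-patient variation to the endpoint. A pre-randomization measurement could remove some of this, but the stated model does not use it. At stake is the precision of the treatment estimate in a trial whose Discussion calls recruitment of 180 patients challenging. The validity of the comparison is not at stake.

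**Working it through.** **Inputs from Sample size calculation.** SD of GFR change 27.8 ml/min (24 pilot patients with B-cell infiltrates); differences of 12 (conservative) and 14.5 ml/min (optimistic: +2.5 against −12); two-sided 5%, 80% power; interim at 116 patients, one-sided 0.005; final one-sided 0.023; 88 per arm. The share of variance explained by Visit 1 eGFR is not given and is varied below.

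**Step 1. Reproduce the plan.** Normal approximation: n = 2 × (1.960 + 0.842)² × 27.8² / 12² = 84.3, so 85 per arm; the exact t calculation gives 86, as stated. For 14.5 ml/min the normal approximation gives 58, as stated (59 by exact t). With looks at 58 and 88 per arm and the stated boundaries, overall one-sided alpha is 0.0245, power at 12 ml/min is 81.1%, and the chance of rejecting at the interim at 14.5 ml/min is 59.2%, against a stated figure of about 60%. The plan's figures hold, and they use the unadjusted SD.

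**Step 2. What the Visit 1 value can explain.** Write

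one-year change = D + C, where D = Visit 1 − pre-rejection and C = one year − Visit 1.

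Var(change) = Var(D) + Var(C) + 2 Cov(D, C).

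The Visit 1 value cancels in the sum. If a drop recovers fully, C offsets D and the drop adds nothing to the endpoint. If a fraction k persists (simple linear model, assumption), the variance that Visit 1 can explain beyond pre-rejection GFR is about k² Var(D).

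**Step 3. Is variation in D plausible?** With the exponent printed in Study assessments, a 20% creatinine rise multiplies eGFR by 1.2^(−1.153) = 0.81. Borderline cases therefore enter at least 19% down, or about 9.5 ml/min at an assumed pre-rejection GFR of 50. Banff IA/IB cases may enter with little or no drop. D therefore probably varies between patients. How much of it persists is not stated.

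**Step 4. Power by further variance explained.** Power = Φ[12 / (27.8 × √(1 − R²) × √(2/88)) − 1.995], with 27.8 × √(2/88) = 4.191.

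| Further R² | Standardized difference | Power |
|---|---|---|
| 0 | 2.863 | 81% |
| 3% | 2.907 | 82% |
| 10% | 3.018 | 85% |
| 20% | 3.201 | 89% |
| 30% | 3.422 | 92% |

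A two-stage calculation agrees: 81.1% at a partial correlation of 0, 82.6% at 0.2 (R² 4%), 84.6% at 0.3 (9%), 87.3% at 0.4 (16%) and 90.7% at 0.5 (25%).

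**Step 5. What each row requires.** The persisting drop needs an SD of √R² × 27.8: 8.8, 12.4 or 15.2 ml/min for 10%, 20% or 30%. If half of each drop recovers, the drop itself needs an SD of 17.6, 24.9 or 30.5. With a drop SD of 10 and half recovered, R² = 5² / 27.8² = 3%, which is the low-gain row.

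**Step 6. Validity.** A null simulation (5,000 runs, 88 per arm; assumed pre-rejection GFR 50 with SD 15, drop SD 12 with 80% persisting, residual SD 25; center not modelled) gave a two-sided type I error of 4.8% with and without the Visit 1 covariate. Both estimates were centred on zero. The mean standard error fell from 4.04 to 3.78, a variance reduction of 1 − (3.78/4.04)² = 12% under those assumptions.

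**The case against.** The strongest reply is that nothing is wrong with the stated model. ANCOVA on baseline, treatment and center is valid and unbiased. The sample size rests on the unadjusted SD, so the planned power needs no covariate. The expected power gain is met, at least in direction, by adjusting for pre-rejection GFR. All of this stands. A reader might infer from the omission that the trial is biased or underpowered; Steps 1 and 6 show that it is neither.

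A reader might also take the whole early drop as noise in the endpoint. Step 2 shows that only the unrecovered part counts. Background puts non-response to steroids at about 20% and says function may return to baseline values, and the 27 pilot patients without B-cell infiltrates averaged 2.5 ml/min above their pre-rejection level at one year. Recovery is not universal, however: the 24 with infiltrates, who resemble the trial population, averaged 12 ml/min below. Some association is plausible, but nothing in the document shows that Visit 1 eGFR is a strong covariate.

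The SD of 27.8 is raw, not the residual after adjustment for baseline and center. The 81% starting point is therefore likely to be somewhat low, and pre-rejection GFR may already absorb part of the drop. Creatinine-based eGFR may also be unstable during acute rejection. These points reduce the gain but do not remove the reason to adjust.

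The analysis plan is not shown and could add the term. The article nevertheless states a specific covariate list, and the point is addressed to that list.

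**Conclusion.** The point holds as a free improvement in precision. A pre-randomization eGFR is available and is omitted from a stated covariate list, so the unrecovered part of the rejection-related loss remains in the error term. There is no bias, no inflation of the type I error and no shortfall against the stated 80% power.

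The gain is unknown. On the assumptions of Step 4 it runs from nothing, through about one percentage point of power at 3% further variance explained, to about eleven points at 30%. The document does not favour any row, and the upper rows should not be read as expected values.

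A case for Banff category as a further required covariate is not supported. It partly overlaps with Visit 1 eGFR through the creatinine rule for borderline cases, rejection grade already has a planned subanalysis, and no separate gain can be shown.

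**What to change.** In Statistical analysis, pre-specify eGFR from the Visit 1 pre-randomization sample as an additional covariate in the primary ANCOVA, alongside pre-rejection GFR and center. State which sample is used and whether it precedes the first steroid bolus; it is a valid covariate either way, because it precedes the randomized treatment. Make the change before the first unblinded look, and use the same model at the interim and final analyses. Banff category (borderline, IA, IB) may be added, but this is optional.

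The endpoint, the treatment contrast, the visits and the sample size stay as they are. The cost is one sentence and about one degree of freedom. If Visit 1 eGFR turns out to explain nothing further, that degree of freedom is all that is lost.

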## Discussion

Acute T-cell mediated tubulointerstitial rejections occur in 15 to 30% of all transplanted patients. In approximately 30% of these cases, B-cell infiltrates are detectable, which may be associated with less beneficial transplant outcomes. However, the current standard therapy for acute rejections focuses on T-cells.

The RIACT study, therefore, tests the hypothesis that additional treatment of the rejection with rituximab is more efficacious than the standard treatment with steroid boli alone. This novel therapy will be studied in a multi-center randomized, placebo controlled, double blind trial with a sufficient number of patients. The recruitment of 180 eligible patients will be challenging despite the multi-centric approach with 13 participating centers. Should the recruitment rate prove to be lower than expected in the first six months after the study begins, more centers will be asked to participate. If this study proves that rituximab is beneficial in acute rejections that contain B-cell infiltrates with regard to the long-term allograft function and without a significant increase in adverse events, future protocols for the treatment of acute rejection most likely will have to incorporate the concept of B-cell targeting.

## Trial status

The study is recruiting patients.

## Abbreviations

FACS: Fluorescence activated cell sorting; GCP: Good clinical practice; GFR: Glomerular filtration rate; IF/TA: Interstitial fibrosis and tubular atrophy; ITT population: Intention-to-treat population; RIACT-study: RItuximab in Acute Cellular tubulointerstitial rejection with B-cell infiltrates in renal Transplant patients.
